# Determining the impact of 24/7 phone support on hospital readmissions after aortic valve replacement surgery (the AVRre study): study protocol for a randomised controlled trial

**DOI:** 10.1186/s13063-017-1971-y

**Published:** 2017-05-30

**Keywords:** Thoracic surgery, Patient readmission, Clinical trial

## Abstract

**Background:**

Patients undergoing surgical aortic valve replacement (sAVR) have high rates of 30-day readmissions. They also report a low health-related quality of life (HRQOL) and elevated anxiety and depression. The aim of the AVRre study is to determine the efficacy and cost of a 24/7 phone-support intervention in reducing post-discharge readmissions after sAVR. The nature of the support is to help patients better understand and self-manage non-urgent symptoms at home.

**Methods/design:**

AVRre is a prospective, randomised controlled study comprising 30 days of continuous phone-support intervention and then intermittent follow-up for the first 12 months. Phone call data from and to patients are evaluated qualitatively; thus, the study has a mixed-method design. Two hundred and eighty-six patients, aged >18 years, scheduled for a sAVR — singly or in combination with another procedure — are recruited from locations in southeast Norway. Patients are randomly assigned to the intervention group, who are purposively phone-called individually 2 and 9 days after discharge and offered on-demand 24/7 (around-the-clock) telephone support for 30 days post-discharge. The primary outcome variable is the number of 30-day hospital readmissions. Secondary outcomes are anxiety and depression symptoms, as measured by the Hospital Anxiety and Depression Scale, HRQOL and quality-adjusted life years, measured by the EuroQol (EQ-5D). Intervention and hospital readmission (diagnosis-related groups (DRGs)/length of stay) for the first year after initial discharge from hospital are used for a cost-utility analysis. Standard parametric and non-parametric tests are used for evaluations over time. Analysis of covariance is used to control for possible differences at baseline. Narratives from phone calls are transcribed verbatim and analysed using systematic text condensation.

**Discussion:**

A complex ‘around-the-clock’ intervention within a university hospital-based setting could be an effective strategy to reduce the high readmission rates to hospital after sAVR. Furthermore, the AVRre 24/7 phone-support manual can be adapted to other high-risk surgery populations with high readmission rates.

**Trial registration:**

ClinicalTrials.gov, NCT02522663. Registered on 11 August 2015.

**Electronic supplementary material:**

The online version of this article (doi:10.1186/s13063-017-1971-y) contains supplementary material, which is available to authorized users.

## Background

Severe aortic stenosis that demands surgical aortic valve replacement (sAVR) due to considerable morbidity and mortality is increasing in prevalence as the elderly population increases globally [1]. sAVR remains the definitive treatment for aortic stenosis (AS), and sAVR has an estimated annual incidence of 85,000 cases [1] in the USA and 1500 cases in Norway (unpublished data from Norwegian Heart Surgery). Irrespective of good immediate surgical outcomes, sAVR patients are characterised by high rates of 30-day readmissions to hospital after discharge. For example, the rates are 19.6% in a US population [2] and 26% in a Danish population [3], and from unpublished register data in Norway (Norwegian Patient Registry, AVR patients’ readmission to hospital, 2011–2014, the Norwegian Directorate of Health 2016), it is estimated to be 22.4% in Norway. Reasons for 30-day readmissions after sAVR are available in two studies. In an American study, heart failure, cardiac rhythm disorders, stroke or transient ischaemic attack, pneumonia, pneumothorax/pleural effusion and gastrointestinal bleeding were reported [4]. In a Danish study, atrial fibrillation, pericardial effusion, congestive heart failure and pneumonia were the most dominant reasons for 30-day readmissions; these conditions occurred acutely in 25% of cases [3]. One in five patients in a study after major surgery was readmitted to a non-index hospital. The use of an index hospital with specialised competence, versus non-index re-hospitalisation, resulted in significantly lower in-hospital mortality [5].

Readmission to hospital in Norway is defined as an unplanned, emergency admittance 8 hours to 30 days after discharge from hospital, accompanied by at least one overnight stay with the readmittance [6]. The majority of patients (96%) discharged approximately 1 week after complex sAVR return home intending to be responsible for their own physical and mental health and for arranging follow-up by their general practitioner (GP) when needed. However, following discharge, patients/inhabitants and partners experience insecurity and the psychological and physical burdens associated with potential readmissions. Moreover, the estimated cost of readmissions is 2 billion Norwegian kroner (NOK) each year, with an estimated readmission rate of approximately 20% [6].

The clinical experience of specialists and municipal healthcare services reveals that standard care at discharge does not typically include patient education. Two systematic reviews and meta-analyses of randomised controlled trials (RCTs) that sought to reduce 30-day hospital readmissions for different diseases concluded that no single intervention (e.g. education, telephone follow-up) was associated with reduced risk for 30-day re-hospitalisation [7, 8]. For example, Melton et al. (2012) suggested a two-time telephone follow-up after discharge during office time [9]. More complex, high-methodological quality interventions, ones in which patients are educated and receive support for self-care, are recommended for preventing hospital readmission and increasing health-related quality of life (HRQOL) status, which otherwise is poorly self-reported [3].

Research on readmission after heart surgery highlights a great need for interventions to be implemented during the first 30 days after discharge to ensure that patients receive quality healthcare and engage in safe practices [3, 5, 10–13]. In a Norwegian home-based intervention the first month after cardiac surgery (*n* = 185), patients and relatives pointed to several negative factors, including lack of information at discharge, insecurity and lack of a ‘connection’ to the index hospital. This was especially true in the first month after surgery, if complications such as pleural effusion and arrhythmias appeared post-discharge [14].

Furthermore, the Norwegian patient experience surveys (2016) report that almost 50% of patients received incomplete information related to discharge preparation, especially regarding what symptoms to expect after discharge, and how and whom to contact if complications occur [15]. These experiences may contribute to feelings of anxiety in patients. Indeed, approximately 29–61% of all patients experience moderate to severe levels of anxiety and depression during the first month after cardiac surgery, with symptoms remaining elevated up to 6 months following surgery [16, 17]. These factors deserve our attention, because anxiety and depression are predictors of morbidity and mortality after heart surgery [18–21]. Therefore, one can hypothesised that interventions that target patients’ and relatives’ need for information and follow-up during the first month after cardiac surgery and the provision of these interventions around the clock could avoid unnecessary hospital readmissions. Indeed, a 24/7 follow-up service by phone goes beyond the results of regular telephone follow-up during office time. No study has tested the effect of an around-the-clock follow-up intervention, where the patients’ needs and symptoms are the base for the intervention. Expert healthcare professionals will be able to assess worsening of symptoms on the phone before a critical stage, and patients can be advised to contact a GP. Telephone follow-up also allows for inclusion of patients who live a long distance from both index and non-index hospitals.

This paper presents the detailed protocol for the AVRre study, in which we aim to determine the efficacy and cost utility of 30-day around-the-clock, 24/7 phone-support intervention after discharge for sAVR. The study’s design and protocol are in accordance with the current Standard Protocol Items: Recommendations for Interventional Trials (SPIRIT) guidelines [22]. A SPIRIT checklist is available online for this manuscript (see Additional file 1). Results will be reported following the CONsolidated Standards Of Reporting Trials (CONSORT) guidelines for non-pharmacological interventions [23, 24].

## Study objectives

### Primary objective

The primary objective of this study is to determine whether a 30-day, around-the-clock, 24/7 phone-support intervention reduces the number of hospital readmissions 30 days after discharge from hospital. The intervention begins immediately after initial discharge, and the outcomes of patients in the intervention are compared to a control group, which receives usual care.

### Secondary objectives

The secondary objectives of the study are as follows:To determine whether an around-the-clock, 24/7 phone-support intervention implemented within 30 days after discharge reduces objectively measured symptoms of anxiety and depression compared to a control group in the first year after discharge from hospitalTo determine whether the around-the-clock, 24/7 phone-support intervention implemented within 30 days after discharge improves HRQOL and quality-adjusted life years (QALYs) compared to the control group in the first year after discharge from hospitalTo perform an economic evaluation specifically to (1) determine the cost utility of the intervention compared to usual care in the study population and (2) assess the cost of readmission to hospital and the cost of GP consultations during the first year after discharge for the intervention and the control groups

## Methods/design

### Study design

AVRre is a prospective, randomised controlled trial (RCT), comprising 30 days of intervention and 12 months of follow-up. The main study began in August 2015. As the intervention consists of phone calls from patients to hospital and vice versa, the design of the study includes an explorative, qualitative component. Thus, this study employs a mixed-method study design. Supporting material for the AVRre study is provided in Additional file 2.

### Study population, recruitment, randomisation and follow-up

Patients eligible for study participation are 18 years or older and are referred for sAVR surgery for the first time at Oslo University Hospital, at either the Ullevål or Rikshospitalet locations, the largest hospitals in southeast Norway. Consecutively admitted sAVR patients are asked by project nurses to participate, and they are included if they meet the following criteria: (1) the surgery is an elective treatment with a single AVR (biological (b) or mechanical (m), an AVR (b or m) + aortocoronary bypass or an AVR (b or m) + supracoronary tube graft; (2) the patient can understand, speak and write the Norwegian language and (3) can be contacted by phone after discharge from hospital. Exclusion criteria are the following: (1) the patient has been admitted to an intensive care unit (ICU) for more than 24 hours; and/or (2) has complications related to surgery (e.g. surgery caused cerebral insult with significant impact on cognitive functions).

One to three days before the planned sAVR, patients arrive at hospital for preoperative preparations. During this time, the project nurse informs the patients about the aim and process of the study. The patients are then given the informed consent form and the baseline questionnaires for review and are given time to consider participation in the study. Patients are contacted a second time before surgery to answer any questions about the study and to deliver further information about the study.

After the patient has provided written informed consent, patient assignment to either usual care (control) or intervention is accomplished by a web-based randomisation system developed and administered by the Unit of Applied Clinical Research, Institute of Cancer Research and Molecular Medicine, Norwegian University of Science and Technology, Trondheim, Norway. This system has been approved by the Data Protection Officer at Oslo University Hospital as complying with human experimental subject protections. Randomisation (1:1 ratio) is performed consecutively with block randomisation and varying size of the blocks to make it impossible to predict to which group the patients are likely to be allocated. Randomisation is done without stratification to the two cardiothoracic sites of the study hospital (i.e. Ullevål or Rikshospitalet).

Before standard discharge from the university hospital to the patient’s local hospital on the fourth day post-sAVR, the project coordinator ([name]) informs the patient verbally and in writing (with a leaflet) to which group he/she has been allocated. For both the control and the intervention groups, the follow-up assessment takes place 1 month (T1), 3 months (T2), 6 months (T3) and 12 months (T4) after discharge from hospital. Follow-up consists of mailing by postal questionnaires with prepaid stamps for return post after completion (see the patient flow and data collection chart of Fig. 1).

**Fig. 1 Fig1:**
[figure not shown]
Patient flow and data collection chart

### Usual care

Preoperatively, all patients recommended by a thoracic surgeon to have aortic valve replacement surgery receive information on expected HRQOL improvement, longer life expectancy and possible complications of surgery. Currently in Norway, at discharge, there is no standard information or post-discharge telephone support in usual care, not from nurses, doctors, university hospitals or local hospitals. There is no blinding in the study.

### Intervention: two components

A brief description of the development of the 24/7 phone-support manual and an example section of it is available online (Additional file 1). The intervention consists of two components.

#### Component 1

Patients in the intervention group are purposely called on days 2 and 9 after discharge by the project coordinator to proactively assess the patient’s present condition and to determine if the patient has questions or if problems have emerged. Details in the patient’s medical history are compiled in advance and reviewed prior to the phone calls, and each structured call relays reminder information to the patient about the availability of the 24/7 phone-call service as part of the intervention. The project coordinator emphasises the importance of daily physical activity [3] and how it has a positive effect on rehabilitation, morbidity and mortality after sAVR. When the patient receives a Short Message Service (SMS) one day ahead of the phone call, he/she has the opportunity to respond if the scheduled day or time is inconvenient for them. Data from the phone calls will be collected in a written, standard format. Also, patients will be encouraged to relate their individual responses/experiences/narratives, for example, when they experience anxiety symptoms.

#### Component 2

The intervention group is also offered 24/7 around-the-clock telephone availability during the entire first month post-discharge. Volunteer, expert intensive care nurses on duty in a cardiac ICU have been trained by an interdisciplinary team to answer the calls from sAVR patients during the first month after discharge. One aspect that the ICU nurses make extremely clear is that this 30-day 24/7 phone-support provision is not a replacement for emergency calls to 113 (911 in some countries). For ethical reasons and because of hospital responsibility to the patients, we include some ’red’ responses (i.e. acute or emergency) in the manual. However, we expect that the sAVR patients will call the intervention phone line mostly for non-urgent health information. If a patient’s problems demand advanced expertise, the project nurse will consult the thoracic surgeon or cardiologist on call in hospital to ensure that accurate diagnostics are completed and suggestions for treatment are made. The project coordinator is always available for the ICU nurses to consult, and will take initiative to arrange regular follow-up meetings and interdisciplinary discussion of challenging phone calls.

### Variables, sources and measurement

Patients will be longitudinally assessed five times during the course of the project: before sAVR and 1, 3, 6 and 12 months after discharge for sAVR. Additional file 1 includes a SPIRIT checklist for the schedule of enrolment, intervention and assessments as presented in Fig. 2. The written informed consent form for the AVRre study is included as Additional file 3.

**Fig. 2 Fig2:**
[figure not shown]
SPIRIT schedule of enrolment, interventions and assessments for the AVRre study

### Primary outcome

#### Readmission

Data from the Norwegian Patient Registry (NPR), the Norwegian Directorate of Health and patients’ medical records will be used to gather the numbers of readmissions within 30 days after sAVR discharge. Moreover, data on causes of readmissions (ICD-10 codes), time and location (index and non-index hospital) will be collected.

### Secondary outcomes

Anxiety and depression symptoms are measured using the Hospital Anxiety and Depression Scale (HADS) [25, 26], a standardised, self-report instrument consisting of 14 items in two subscales. The 14 items include seven items for anxiety (HADS-A) assessment and seven for depression (HADS-D). Patients rate themselves on each item from 0 (not present) to 3 (maximum), yielding a total possible score of 21 for each subscale. The psychometric properties of the HADS are well documented in research conducted in many different countries; this includes valid use in heart patients [26].

HRQOL and QALY are assessed using the internationally recognised EQ-5D instrument [27]. EQ-5D is a standardised instrument comprising five dimensions of self-reported health status for clinical and economic appraisal. These dimensions are mobility, self-care, usual activities, pain/discomfort and anxiety/depression. The respondent rates himself on each dimension for the degree (no problem, some problem, extreme problem) that best describes his/her present health status.

#### Economic evaluation

Economic analyses are performed for two reasons. (1) The time it takes to proactively call the patients, as well as the time needed to answer the patient on the intervention phone and the time needed for calling back if consulting the physician at hospital, will be measured and valued. (2) Register data on the cost of readmission to hospital (diagnosis-related groups (DRGs)/length of stay) and the number of GP consultations during 30 days and the first year after discharge will be used for the cost-utility analysis and will be reported as an incremental cost-effectiveness ratio (ICER). Sensitivity analyses will be conducted to measure uncertainty in the estimates. In addition, data from the patients’ medical records are gathered, e.g. comorbidities.

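### The one-year cost-utility analysis lists only readmissions and GP consultations as downstream care and gives no readmission definition that fits a year, so other hospital contacts that may differ between arms can fall outside the ICER

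*Protocol article*

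**What the plan says.** **Cost items.** Three places in the protocol article describe what enters the cost-utility analysis.

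- Economic evaluation: "Register data on the cost of readmission to hospital (diagnosis-related groups (DRGs)/length of stay) and the number of GP consultations during 30 days and"; that sentence continues to the first year after discharge and says the result is reported as an ICER. The same section covers delivery of the service: time for proactive calls, for answered calls, and "the time needed for calling back if consulting the physician at hospital, will be measured and valued". Sensitivity analyses are promised without stating their content.
- Secondary objectives: the economic aim is cost utility against usual care, and to "assess the cost of readmission to hospital and the cost of GP consultations during the first year after discharge" in both groups.
- Abstract, Methods/design: "Intervention and hospital readmission (diagnosis-related groups (DRGs)/length of stay) for the first year after initial discharge from hospital are used for a cost-utility analysis". GP consultations are not named here.

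**Readmission.** The only definition is in the Background, where it is given as the Norwegian one: "an unplanned, emergency admittance 8 hours to 30 days after discharge from hospital, accompanied by at least one overnight stay with the readmittance". Neither the Primary outcome section nor the Economic evaluation section restates it or offers another.

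**Routes of care.** The Background says that callers may be told to see their GP. Component 2 of the intervention adds escalation when a problem needs more expertise than the nurse has: "the project nurse will consult the thoracic surgeon or cardiologist on call in hospital to ensure that accurate diagnostics are completed and suggestions for treatment". It also says that the manual holds some acute or emergency responses. Under Usual care, the control arm has no post-discharge telephone support.

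**The concern.** A cost-utility comparison needs the same costs counted in both arms, and it needs to count the kinds of care that the intervention may change. Here the hospital side of the list is a single item, readmission. Emergency attendances without a stay, day-case treatment, outpatient visits and planned admissions are not listed. The intervention arm alone has a phone line to hospital staff, so its use of such contacts may differ from that of the control arm.

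The item that is listed is also not defined for its purpose. Costs run for a year, while the only definition on paper stops at day 30. An analyst would have to decide, possibly with the data in view, what counts as a readmission in months 2 to 12 and whether same-day or planned stays belong.

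At stake is the ICER, which serves a stated secondary objective and is meant to inform the health service. The primary comparison of 30-day readmissions is not affected by this point.

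**Working it through.** **1. The plan's own figure.** The economic section states no number. The only design calculation is under Sample size and power calculation: 15% against 5%, 143 per group, at least 80% power. With pooled variance under the null and a two-sided 5% level (sidedness is not stated):

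n = [1.960 × √(2 × 0.10 × 0.90) + 0.842 × √(0.15 × 0.85 + 0.05 × 0.95)]² / 0.10² = (0.832 + 0.352)² / 0.01 ≈ 140.1, so 141 per group. Power at 143 per group is 80.8%. The stated size reproduces, and the planned rates can serve as the basis for an illustration.

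**2. Does the readmission definition fit the cost horizon?** Set the two side by side.

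| | Background definition | Economic evaluation |
|---|---|---|
| Window | 8 hours to 30 days | 30 days and first year |
| Type | unplanned, emergency | not stated |
| Overnight stay | required | not stated |

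- If the Background definition governs the costs, no hospital cost after day 30 counts, and same-day or planned contacts never count.
- If it does not govern, readmission has no definition for the one-year cost.

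Either way the text needs a definition that it does not contain.

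**3. What omission does to the saving.** Let R be the cost of one readmission, c the cost of an unlisted hospital contact as a fraction of R, and d the difference per patient (intervention minus control) in unlisted contacts.

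- Saving booked per patient at the planned rates: (0.15 − 0.05) × R = 0.10R. Over 143 patients, 21.45 − 7.15 = 14.3 readmissions, counting one per readmitted patient.
- True hospital saving: 0.10R − d × c × R.
- Error as a share of the booked saving: d × c / 0.10. Positive d means the saving is overstated; negative d means it is understated.

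**4. Substitution.** If a share s of averted readmissions becomes an unlisted contact, then d = 0.10 × s and the overstatement is s × c.

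| s (assumed) | c (assumed) | s × c | Readmission equivalents out of 14.3 |
|---|---|---|---|
| 0 | any | 0% | 0 |
| 0.25 | 0.20 | 5% | 0.05 × 14.3 = 0.7 |
| 0.50 | 0.40 | 20% | 0.20 × 14.3 = 2.9 |
| 1.00 | 0.50 | 50% | 0.50 × 14.3 = 7.2 |

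**5. The opposite case.** If the line instead averts unlisted contacts, with d between −0.025 and −0.05 and the same c, the saving is understated by 0.025 × 0.20 / 0.10 = 5% to 0.05 × 0.40 / 0.10 = 20%.

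The article gives no values for s, c, d, R or the QALY difference, so none of this can be turned into an error in the ICER itself.

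**The case against.** A reader might infer more than the article supports: that the analysis prices only overnight readmissions and GP visits, that any shifted care costs nothing, and that the ICER is therefore biased in favour of the intervention. Four things speak against that.

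- Phone-service time is valued, including call-backs after a physician is consulted.
- The one redirection to outside care that the text spells out, to the GP, is a listed cost.
- The overnight condition is in the Background; the Economic evaluation section does not adopt it, so exclusion of same-day contacts by rule is not shown.
- The article says that a physician is consulted and that diagnostics are completed. It does not say that callers are brought in and sent home the same day. That is a plausible inference, no more.

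Bias also needs a between-arm difference in unlisted contacts. The service aims to help patients manage non-urgent symptoms at home, so it could reduce such contacts, and the error would then run against the intervention.

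These objections stand, and they limit the point. A further one carries less weight: an article condenses, and detailed costing rules may sit in a fuller document. That would excuse silence, but the article gives a cost list in three places, and none goes beyond readmission and GP care for downstream use. The promised sensitivity analyses do not settle the matter either, because they cannot recover contacts that were never extracted.

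**Conclusion.** The point holds as a weakness in the stated costing method. The plan names readmission as the only hospital cost, offers no definition of it that works over a year, and leaves out hospital contacts whose frequency the intervention may change. The incremental cost can then be wrong in either direction.

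The document does not allow the size to be computed. The 5–20% overstatement of the readmission saving rests wholly on the assumed s = 0.25–0.50 and c = 0.20–0.40, on the planned 15% and 5% rates being realised, and on one readmission per readmitted patient. With no substitution it is zero. That the ICER is biased, or biased in the intervention's favour, is not shown.

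The change is worth making because costing all hospital contacts is a better method than the stated list, and registry data are already being collected.

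**What to change.** In Secondary objectives and Economic evaluation, define hospital cost for the ICER as all hospital contacts in both arms from discharge to 12 months: overnight, same-day or emergency, day-case and outpatient, planned and unplanned. Take them from the registry extraction. Add GP consultations and phone-service time, and bring the Abstract's shorter list into line. State that the 30-day readmission definition applies to the primary outcome only.

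The cost is revised wording, a wider registry extract and some extra costing work. Ethical considerations records consent to medical-record and patient-registry data for the cost-utility analysis; whether that consent and the registry approval cover the wider extract has to be confirmed. The estimated saving may turn out less favourable. Randomisation, the intervention and the primary test are unchanged.
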